#### **9.4 Permanent Discontinuation in Response to Adverse Events**

##### **Grade 1 or 2**

In general, a participant who develops a Grade 1 or 2 AE as defined by the DAIDS Table for Grading Adult and Pediatric Adverse Events, Version 1.0, December 2004 (Clarification dated August 2009) regardless of relationship to study medication will continue study medication use.

##### **Grade 3**

For participants who develop a Grade 3 AE as defined by the DAIDS Table for Grading Adult and Pediatric Adverse Events, Version 1.0, December 2004 (Clarification dated August 2009) that is judged by the study investigators to be unrelated to study medication, the study medication will continue. The study medication must be permanently discontinued for participants who develop a Grade 3 AE judged by a physician investigators to be related to the study medication.

##### **Grade 4**

If a participant develops a Grade 4 AE as defined by the DAIDS Table for Grading Adult and Pediatric Adverse Events, Version 1.0, December 2004 (Clarification dated August 2009) and the AE is determined to be related to study medication, then study medication must be permanently discontinued.

Any time a participant is permanently discontinued from study medication (prior to completion of the 12 week course of study medication), HCV resistance testing will be performed.

#### **9.5 HIV-1 Infection**

Participants who are positive for HIV (known or positive at Screening) will not be eligible to participate. If HIV seroconversion occurs during the time of study medication use, the study medication will continue.

#### **9.6 Criteria for Early Termination of Study Participation**

Participants may voluntarily withdraw from the study for any reason at any time. The study investigators also may withdraw participants from the study to protect their safety and/or if they are unwilling or unable to comply with required study procedures. Participants also may be withdrawn if Gilead Sciences, government or regulatory authorities, including the FDA and Office for Human Research Protections (OHRP), or site IRBs/ECs terminate the study prior to its planned end date. Detailed reason with the withdrawal of a participant will be documented in the research record. Every

reasonable effort will be made to continue to follow the participant as scheduled for safety

## **10 STATISTICAL CONSIDERATIONS**

### **10.1 Overview and Summary of Design**

This is a Phase 1, single-arm, open label pilot study of treatment for chronic HCV infection during pregnancy in 15 HCV (genotype 1, 4, 5, and 6)-infected pregnant women with a 12-week course of LDV/SOF FDC.

### **10.2 Study Endpoints**

Pregnant women meeting all of the criteria in section 5.2 and 5.3 will be enrolled into the study and followed prospectively through 12 weeks after the last dose of study medication. Infants will be enrolled upon delivery and followed prospectively through approximately one year of age.

#### **10.2.1 Primary Endpoints: Maternal**

The primary endpoints of the study are primary PK parameters (specifically  $AUC_{tau}$ ,  $C_{max}$ , and  $C_{tau}$ ) of LDV, SOF, and GS-331007 assessed at 3 gestational age time points:

- 1) Late second trimester between 25 + 0 and 26 + 6 weeks' gestation (after at least 10 days of therapy)
- 2) Early third trimester between 29 + 0 and 30 + 6 weeks' gestation and
- 3) Late third trimester between 33 + 0 and 34 + 6 weeks' gestation.

#### **10.2.2 Secondary Endpoints: Maternal**

The secondary endpoints of the study are:

- 1) Secondary PK endpoints of LDV, SOF and GS-331007:
  - a. Total clearance (CL/F)
  - b. Protein binding
  - c. Unbound clearance
- 2) Maternal sustained virologic response after 12 weeks of therapy (SVR12)
- 3) Adverse events including clinical and laboratory changes
- 4) Pregnancy outcomes including the following:
  - a. delivery prior to 37 completed weeks of gestation
  - b. stillbirth or intrauterine fetal demise
  - c. intrapartum hemorrhage
  - d. postpartum hemorrhage
  - e. non-reassuring fetal status
  - f. chorioamnionitis

- g. hypertensive disorders of pregnancy
- h. gestational diabetes
- i. intrauterine growth restriction

### Secondary Endpoints: Infant

Consistent with the secondary study objectives, the following secondary endpoint will be assessed for infants:

- Major malformations, defined as structural abnormalities with surgical, medical, or cosmetic importance.
- Weight, length, and head circumference at birth, 8 weeks, six months and 12 months.
- Neurodevelopmental assessments at 6 months and 12 months as measured by Bayley Neurodevelopment Screening Test.
- Perinatal HCV transmission assessed by presence of HCV RNA at 8 weeks, six months or 12 months.

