**Secondary Endpoints:**

- **Sustained Viral Response (SVR12)**
  - HCV RNA viral load will be assessed at 12 weeks after completion of LDV/SOF treatment. An undetectable viral load will be considered a SVR12
- **Maternal Safety**
  - Safety laboratory assessments of blood counts and liver function will be measured at the PK1 and PK2 visits (approximately 2-4 weeks and 6-8 weeks of treatment)
  - Pregnancy and delivery outcomes collected prospectively
- **Neonate Safety**
  - Major malformations, defined as structural abnormalities with medical, surgical or cosmetic importance
  - Weight, length, and head circumference at birth, 8 weeks, six months and 12 months
  - HCV RNA viral load will be assessed at birth (as available), one to three months, at six months and then again at 12 months only if negative viral loads are not documented at one to three and six months
  - Developmental exams will be performed at six months and 12 months

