## 2.2 Rationale

**Pregnant women would be uniquely motivated to be adherent to the treatment regimen and to not become re-infected postpartum.** The HCV treatment guidelines recommend that priority consideration be given to treatment of Reproductive-aged women who desire pregnancy. A recent meta-analysis of the risk of perinatal HCV infection to children of HCV antibody-positive and RNA-positive women was 5.8% (95% confidence interval [CI], 4.2%-7.8%) for children of HIV-negative women and 10.8% (95% CI, 7.6%-15.2%) for children of women co-infected with human immunodeficiency virus (HIV). Women with chronic HIV infection are more likely to adhere to antiviral treatment during the antepartum period as compared to the postpartum period. A meta-analysis of adherence to antiretroviral therapy during and after pregnancy in low-income, middle-income and high-income countries showed a statistically significant difference in adequate adherence levels 75.5% (95% CI 71.5-79.7%) in the antepartum period as compared to 53.0% (95% CI 32.8-72.7%) in the postpartum period. Many HIV-infected women describe a loss of motivation to continue antiretroviral therapy postpartum and breastfeeding because it is no longer required to protect the child. Additionally, this decrease in motivation was compounded by the overwhelming demands of everyday life. We hypothesize that HCV-infected women will be similarly motivated and will be more likely to adhere to treatment during the antepartum period than outside of pregnancy or in the postpartum period.

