##### **Secondary Endpoints:**

- **Sustained Viral Response (SVR12)**
  - HCV RNA viral load will be assessed at 12 weeks after LDV/SOF treatment completion. An undetectable viral load will be considered a SVR12

- **Maternal Safety**

- Safety laboratory assessments of blood counts, creatinine, liver function, creatinine kinase and lipase will be measured at the PK1 and PK2 visit (approximately 2-4 and 6-8 weeks after initiation of LDV/SOF FDC)
- Pregnancy and delivery outcomes collected prospectively by chart review and participant interview

- **Neonate Safety**

- Major malformations, defined as structural abnormalities with medical, surgical or cosmetic importance
- Weight, length, and head circumference at birth (by exam or chart review), 8 weeks, six months and 12 months
- HCV RNA will be assessed at birth (for participants delivering at MWH), 1-3 months and 6 months, and then again at 12 months only if negative viral loads are not documented at one to three and six months
- Neonatal development assessed by Bayley's development testing at six months and 12 months

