| Medical Record Review for Delivery Outcomes | 
 
• Type of pregnancy outcome
 
• Gestational age at pregnancy outcome
 
• Method of calculation for gestational age at pregnancy outcome
 
• If delivery, type of delivery (e.g., vaginal, vaginal forceps-assisted, vaginal vacuum-assisted, cesarean section)
 
• Complications related to pregnancy outcome 
 
– Delivery complications (e.g., intrapartum and/or postpartum hemorrhage, non-reassuring fetal status, chorioamnionitis)
 
– Other complications not related to a delivery
 
 
 
 |
| Baseline Infant Information**               | 
 
• Sex
 
• Weight
 
• Length
 
• Head circumference
 
• Apgar scores
 
• Medical history (e.g., sepsis, respiratory distress, any abnormalities noted on infant exam)
 
• Medication history
 
                                                                                                                                                                                                                                                                                                                                          |
| Laboratory***                               | 
 
• Maternal HCV RNA viral load
 
• Cord blood collection for HCV RNA viral load
 
• Cord blood collection for PK analysis (if still on study medication)
 
• Maternal plasma sample for PK analysis (if still on study medication)
 
• Maternal protein binding assay (if still on study medication)
 
• Cord blood protein binding assay (if still on study medication)
 
                                                                                                                                                                     |

\*Unless participant intends to breastfeed, in which case study medication will be discontinued

\*\*All Baseline Infant Information may be extracted from the infant medical record as available

\*\*\*Laboratory tests performed as applicable for participants who deliver at Magee-Womens Hospital

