| Laboratory                           | 
 
• Collect infant blood 
 
– HCV RNA (iV1, iV2, and as applicable at iV3)*
 
– HCV resistance testing (if HCV RNA is detectable)
 
 
 
                                                                                                                                     |

\*If HCV RNA is detectable at iV1 or iV2, the infant would need to return to have HCV resistance testing done and would also have an HCV RNA performed at iV3. If HCV RNA is non-detectable/negative at both iV1 and iV2, no additional samples are needed.

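### As worded, the perinatal transmission endpoint makes an infant a case on one detectable HCV RNA result and does not use the repeat samples already scheduled

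*Protocol*

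**What the plan says.** Section 10.2.2 lists, among the infant secondary endpoints, "Perinatal HCV transmission assessed by presence of HCV RNA at 8 weeks, six months or 12 months". It sets no requirement for a second detectable result and no rule for a positive followed by negatives.

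Table 8 (Section 7.4.5) sets out what follows a positive: "If HCV RNA is detectable at iV1 or iV2, the infant would need to return to have HCV resistance testing done", and the infant "would also have an HCV RNA performed at iV3". If iV1 and iV2 are both negative, no further sample is needed. The Protocol Summary and Section 4.2 also call for the 12-month sample when negative results at the two earlier time points are not documented, so a missed visit leads to iV3 as well.

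The timing of the first postnatal sample is given in three ways: 8 weeks in Section 10.2.2; one to three months in the Summary, Section 4.2 and Appendix II; and 8 weeks ± 6 weeks in Table 1 and Section 7.4.5. Table 1 adds that the windows are targets and that a visit outside them is not a deviation.

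A birth sample appears in the neonatal safety lists. The Summary has "HCV RNA viral load will be assessed at birth (as available), one to three months, at six months", and Section 4.2 has "HCV RNA will be assessed at birth (for participants delivering at MWH), 1-3 months and 6 months". The Delivery Visit table shows what it is: "Cord blood collection for HCV RNA viral load", done only for deliveries at the study hospital. Section 10.2.2 does not mention birth in the transmission item, although it names birth for the growth measurements.

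**The concern.** The time points are joined by *or*, so the endpoint is met at the first detectable result and nothing later can reverse it. An infant detectable at iV1 and undetectable at iV2 and iV3 is reported the same way as an infant detectable at all three. The schedule takes the trouble to repeat the test after a positive, yet the endpoint makes no use of the answer.

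With about 15 infants, the reported count will be zero or very small. A single early result that is never reproduced would then account for the whole reported rate, and a reader of the summary could not tell it from an established infection.

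**Working it through.** The Protocol states no expected count, power or target for perinatal transmission, so there is no figure to reproduce. The check has three parts.

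**1. Classification under the wording as it stands**

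| iV1 | iV2 | iV3 | Section 10.2.2 as written | At least two postnatal positives |
|---|---|---|---|---|
| neg | neg | not required | not a case | not a case |
| pos | pos | either | case | confirmed |
| pos | neg | pos | case | confirmed |
| pos | neg | neg | case | unconfirmed, listed |
| neg | pos | neg | case | unconfirmed, listed |
| pos | lost | lost | case | indeterminate, listed |
| missed | missed | pos | case | lone iV3 positive, listed |

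The two rules differ only in the last four rows. In the rows with a positive then a negative, the samples needed to decide are already in the schedule.

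**2. Weight of one result**

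Inputs: 15 infants (Protocol Summary, sample size) and the background risk cited in Section 2.2, "5.8% (95% confidence interval [CI], 4.2%-7.8%) for children of HIV-negative women".

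- Expected infections at the cited risk: 15 × 0.058 = 0.87. Over the cited interval: 15 × 0.042 = 0.63 to 15 × 0.078 = 1.17.
- One case: 1/15 = 6.7%. Exact (Clopper-Pearson) 95% limits: lower 1 − 0.975^(1/15) = 0.2%; upper, the 97.5th percentile of Beta(2, 14), = 31.9%.
- No case: 0/15 = 0%, with upper limit 1 − 0.025^(1/15) = 21.8%.

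One unreproduced result therefore moves the point estimate from 0% to 6.7%, close to the cited background risk. The two intervals overlap almost entirely.

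**3. How often this could happen (illustrative)**

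The Protocol gives no rate for isolated positives. **Assumption:** each sample from an uninfected infant has probability f of an isolated detectable result, independently, with f from 0.2% to 2%; all 15 infants are uninfected and attend iV1 and iV2.

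- *Any positive.* If iV1 and iV2 are both negative, iV3 is not tested, so two samples matter. Per infant: 1 − (1 − f)². At least one of 15: 1 − (1 − f)^30, which is 5.8% at f = 0.2% and 45% at f = 2%. (This 5.8% matches the background risk only by coincidence.)
- *At least two positives among iV1, iV2 and the triggered iV3.* Per infant: f² + 2f(1 − f)·f = 3f² − 2f³, which is 0.000012 at f = 0.2% and 0.001184 at f = 2%. At least one of 15: 0.018% and 1.8%.

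The direction is robust. The absolute values depend wholly on the assumed f and on independence.

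**The case against.** The strongest reply is that Section 10.2.2 says how transmission is assessed and stops short of a formal case definition; the neighbouring item on malformations does use the language of definition. The *or* may only reflect that the 12-month sample is conditional, since *and* would be wrong. Classification of discordant serial results is often left to an analysis plan, which may exist. For a safety endpoint in 15 infants a sensitive rule is also defensible, because each positive would be looked at individually and a stricter rule could hide a signal.

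Part of this stands. A sensitive count should be kept, and the fix keeps it. But the Protocol does fix a rule, and on its plain reading a later negative has no effect. An analysis plan that required confirmation would depart from that text.

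Three stronger readings are tempting and are not supported:

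- *A reader might infer that the sections contradict each other on whether a positive cord-blood result is a case.* The Summary and Section 4.2 only list when HCV RNA is measured. Section 10.2.2 alone names transmission, and it leaves birth out. Collecting a sample that the endpoint does not use is not a contradiction. It follows that case ascertainment does not depend on the delivery hospital. The Protocol does not discuss contamination of cord blood.
- *A reader might infer that 1/15 would be taken as showing no benefit.* Section 10.5 plans no comparison with 5.8%, which appears only as background. With limits of 0.2% to 31.9%, 1/15 shows neither benefit nor its absence, and 0/15 (upper limit 21.8%) could not show benefit either.
- *A reader might infer that transmission is the main reason for the trial.* No objective names it. Section 13.3.2 mentions its prevention only as possible future guidance.

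**Conclusion.** The point holds as a minor one. On its plain reading, Section 10.2.2 counts an infant as infected on one detectable postnatal result, possibly at about 2 weeks of age (8 − 6 weeks), whatever iV2 and the triggered iV3 show. The size is one infant: 0/15 becomes 1/15, or 6.7% (exact 95% CI 0.2% to 31.9%). This rests on a denominator of 15; replacements or losses would change it slightly. The likelihood of such a result cannot be taken from the documents, and the ranges shown are illustrative only.

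The birth sample and the differing descriptions of the first postnatal visit are matters of clarity and do not change the endpoint. It is a descriptive secondary endpoint. The sample size and the primary pharmacokinetic analysis are untouched.

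**What to change.** In Section 10.2.2:

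1. Define confirmed perinatal transmission as HCV RNA detected in at least two separate postnatal infant samples, using the iV1, iV2 and iV3 samples already scheduled.
2. Report beside it the number of infants with any postnatal positive, so that the stricter rule hides nothing.
3. List individually each infant with one positive followed by negatives, one positive and then loss to follow-up, or a lone iV3 positive after missed visits.

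For consistency, state in the Summary and Section 4.2 that the birth (cord-blood) result, collected only for study-hospital deliveries, is descriptive and not part of the Section 10.2.2 endpoint. Use one description of the first postnatal time point in Section 10.2.2, the Summary, Section 4.2, Table 1, Section 7.4.5 and Appendix II.

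The cost is wording only, with no added visit or blood draw. The downside is that an infant lost after one positive is indeterminate in the confirmed count, though still visible in the any-positive count and the listing.

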## **10.4 Participant Accrual and Retention**

Pregnant and chronically HCV-infected women who meet the criteria outlined in Section 5 and are interested in participating, will be enrolled into this study. Once a participant is enrolled, the study staff will make every reasonable effort to retain her for the entire study period. A maximum of 7% (one woman and child) loss-to-follow-up will be targeted.

## **10.5 Data Analysis**

### **10.5.1 Analysis of SOF and LDV concentrations**

Between-group comparisons will evaluate changes in SOF and LDV PK parameters between the historical controls (nonpregnant women of reproductive age) compared to the 15 pregnant women stratified by gestational age. Area under the time concentration curve over a dosing interval ( $AUC_{tau}$ ), maximum concentration ( $C_{max}$ ), and minimum concentration ( $C_{tau}$ ) will be calculated by gestational age. The PK parameters of the pregnant women at different gestational ages will be compared to the historical control group by calculating the geometric mean ratios and 90% CIs. Drug concentrations will be summarized descriptively (mean, median, minimum, maximum, standard deviation) by gestational age.

### **10.5.2 Analysis of SVR12**

Outside of pregnancy, 96% of patients treated with LDV/SOF for 12 weeks obtained an SVR12. In this pilot study, we estimate that at least 14 out of the 15 chronically HCV-infected pregnant women will have a SVR12 after treatment. Participants who do not complete the treatment course or report low adherence will be excluded from the analysis.

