| Sample Size:      | 15 women and their infants (participants who do not complete treatment or report less than 85% adherence will be replaced)                                                                                                                                                                                                                                                              |
| Study Population: | Pregnant women diagnosed with genotype 1, 4, 5, or 6 chronic hepatitis C infection that are between the ages of 18 and 39 and are 14 + 0 and 22 + 6 weeks of gestation at Screening                                                                                                                                                                                                     |
| Study Site:       | Magee-Womens Hospital of UPMC, Pittsburgh, PA                                                                                                                                                                                                                                                                                                                                           |
| Study Design:     | Single-site, single-arm pilot study                                                                                                                                                                                                                                                                                                                                                     |
| Study Duration:   | Approximately 28 weeks per maternal participant and one year of infant follow up.                                                                                                                                                                                                                                                                                                       |
| Study Medication: | Fixed-dose combination tablet of Ledipasvir 90 mg and Sofosbuvir 400 mg (LDV/SOF FDC)                                                                                                                                                                                                                                                                                                   |

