#### **5.1.2 Retention**

The importance of retention will be stressed to the participant at each visit as part of protocol adherence counseling. Once a participant is enrolled, the study staff will make every effort to retain the participants in follow-up to minimize possible bias associated with loss-to-follow-up. Any participant that discontinues the study before the PK3 visit is completed or if a participant reports missing more than 1 dose per week averaged over the duration of the study then they will be replaced by recruiting another participant into the study. We anticipate needing to replace no more than two participants.

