## 7.5 Follow-up Procedures for Participants Who Permanently Discontinue Study Medication

Participants will be permanently discontinued for significant laboratory abnormalities or adverse events as outlined in section 9.3 and 9.4, if they miss greater one dose per week (averaged over the duration of the study), or if they choose to discontinue the study medication. Participants who are permanently discontinued from the study will be instructed to return the study medication and study medication log. All protocol-specified study procedures will continue for safety except the following:

- Provision of study medication
- Provision of medication use adherence counseling

The following procedures will be performed at the visit in which study medication use is permanently discontinued:

- Collection of blood for PK analysis (single time point)
- HCV resistance testing
- Viral load as needed (i.e. participant withdraws, investigator opinion)
- Medical history review
- Concomitant medication review
- Brief physical examination including vital signs, if indicated.

The participant will be asked to continue in the study and complete all remaining scheduled maternal and infant visits per protocol for safety.

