### **9.3 General Criteria for Permanent Discontinuation of Study Medication**

A participant will be permanently discontinued from medication use by the physician investigators for any of the following reasons, according to the HCV treatment guidelines:

- 5-fold or greater increase in ALT or AST at the PK1 or PK2 visit compared to baseline result (Screening visit), confirmed by immediate repeat testing
- Any increase of ALT or AST of less than 5-fold from baseline (Screening visit) at the PK1 or PK2 visit that is accompanied by any weakness, nausea, vomiting, or jaundice
- 3-fold or greater increase in ALT or AST accompanied by bilirubin >2x the upper limit of normal, confirmed on immediate repeat testing
- Increase HCV RNA viral load by greater than 10-fold at PK2 visit (6-8 weeks after starting treatment)
- Participant is unable or unwilling to comply with required study procedures
- If the participant delivers prematurely (and is still on study medication) and desires to breastfeed
- Participant might be put at undue risk to their safety and well-being by continuing medication use, according to the judgment of the study investigators. The study investigators will consult with the independent safety physician prior to all study medication discontinuation instituted for this reason.

Any time a participant is permanently discontinued from study medication (prior to completion of the 12 week course of study medication), HCV resistance testing will be performed.

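### The SVR12 analysis drops women who stop treatment early or report low adherence, including any stopped for virologic breakthrough, so failures of that kind leave the denominator

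*Protocol*

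**What the plan says.** The SVR12 rule is in Protocol Section 10.5.2: "Participants who do not complete the treatment course or report low adherence will be excluded from the analysis". The same section cites 96% outside pregnancy and expects at least 14 of 15 women to reach SVR12.

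Several routes lead to non-completion or low adherence:

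- **Virologic (9.3):** "Increase HCV RNA viral load by greater than 10-fold at PK2 visit (6-8 weeks after starting treatment".
- **Liver enzymes (9.3):** specified ALT or AST rises.
- **Delivery (9.3):** premature delivery on study medication with a wish to breastfeed.
- **Adverse events (9.4):** "The study medication must be permanently discontinued for participants who develop a Grade 3 AE judged by a physician investigators to be related", and likewise for related Grade 4 events.
- **Missed doses (7.5):** medication is stopped permanently "if they miss greater one dose per week (averaged over the duration of the study").

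On replacement, the Protocol Summary says that "participants who do not complete treatment or report less than 85% adherence will be replaced". Sections 5.1.2 and 10.3 are narrower: "Any participant that discontinues the study before the PK3 visit is completed or if a participant reports missing more than 1 dose per week". The missed-dose limit there is a mean across the study.

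On follow-up after stopping, Section 7.5 says: "The participant will be asked to continue in the study and complete all remaining scheduled maternal and infant visits per protocol for safety". Section 7.4.4 times V7 at 12 weeks from the last dose and draws HCV RNA there.

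**The concern.** Whether a woman enters the SVR12 denominator depends on events after treatment starts, and one of those events is a form of the outcome. Breakthrough on treatment is a failure of viral response, yet under Sections 9.3 and 10.5.2 together it takes the woman out of the analysis of viral response. Replacement can bring the reported number back to 15, so the loss need not be visible in the result.

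This matters for what the pilot is meant to learn. Section 2.5 asks whether the viral response resembles that of nonpregnant women, given higher viral loads in pregnancy. Section 13.3.1 warns that the dose may be inadequate in pregnancy and that resistance may follow. Breakthrough and early stopping would be the signals of that risk, and they are the cases left out of the rate.

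The rate is also set beside a 96% figure that was not obtained by the same exclusion.

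**Working it through.** **1. The plan's own figure.** Inputs from 10.5.2: n = 15, rate 0.96.

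- Expected responders: 15 × 0.96 = 14.4.
- P(at least 14 of 15) = 15 × 0.96^14 × 0.04 + 0.96^15 = 0.339 + 0.542 = 0.881.

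The expectation of at least 14 of 15 agrees with 96%.

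**2. What the 96% counts.** Inputs are the three 12-week LDV/SOF arms without ribavirin in Table 2:

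| Trial | Total | SVR12 | Listed treatment failures |
|---|---|---|---|
| ION-1 | 214 | 211 | 1 |
| ION-2 | 109 | 102 | 7 |
| ION-3 | 216 | 206 | 3 |
| Sum | 539 | 519 | 11 |

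- 519/539 = 96.3%, which reproduces the 96%.
- Without SVR12: 539 − 519 = 20. Not listed as treatment failures: 20 − 11 = 9. These 9 stay in the denominator; Table 2 does not give their reasons.
- For genotype 4, Section 2.4.1 is explicit: a participant who withdrew consent is kept in the denominator (20/21). With 21/22 from the other study this is 41/43 = 95%, the figure quoted in Section 2.1.

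**3. Effect of the denominator.** Section 5.1.2 anticipates no more than two replacements. Exact (Clopper-Pearson) 95% intervals, counting each excluded woman as a non-responder (the worst case):

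| Reported | One excluded | Two excluded |
|---|---|---|
| 15/15 = 100% (78.2-100) | 15/16 = 93.8% (69.8-99.8) | 15/17 = 88.2% (63.6-98.5) |
| 14/15 = 93.3% (68.1-99.8) | 14/16 = 87.5% (61.7-98.4) | 14/17 = 82.4% (56.6-96.2) |

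If both excluded women respond, 15/15 becomes 17/17 and there is no bias.

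**4. Direction.** Let q be the excluded share, and let C and X be the SVR12 rates in completers and excluded women. All-treated rate = (1 − q)C + qX, so the completer rate exceeds it by q(C − X). With q = 2/17 = 0.118 and C = 0.96 (assumed):

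- X = 0: all-treated 84.7%, excess 11.3 points.
- X = 0.5: 90.6%, excess 5.4 points.
- X = 0.96: 96.0%, excess 0.

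**5. Is the replaced set the excluded set?** Twelve weeks from a start at 23+0 to 24+6 end at 35+0 to 36+6, after the PK3 window closes at 34+6. A woman who stops between PK3 and the end of her course is excluded from SVR12 and is replaced under the Protocol Summary. Under 5.1.2 and 10.3 she is not replaced unless she also missed too many doses. The adherence limits themselves nearly agree: one missed dose per week is 6/7 = 85.7%, against 85%.

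**The case against.** The strongest defence is that a completer estimate fits the way the endpoint is framed. The Protocol Summary defines SVR12 by virus twelve weeks after completing 12 weeks of treatment, and the study is a Phase 1 PK pilot in which SVR12 is secondary, with no test, margin or decision rule. The 96% supports an expected count, not a planned comparison. The data for an all-treated rate would be collected anyway. All of this stands, and it limits the severity. It does not justify removing a woman from a viral response rate because her virus rebounded. Nor is the gap one that a statistical analysis plan would merely fill: the protocol itself states the exclusion.

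Several stronger readings are tempting, and the protocol does not support them:

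- **That treatment failures in general leave the denominator.** A woman who completes treatment with acceptable adherence and is viraemic at V7 is still counted as a failure. The virologic rule acts only at PK2 and only for a rise above 10-fold.
- **That 15/17 is the corrected rate.** It is the worst case. Women who stop early may still respond: Table 2 shows 202/215 = 94% after an 8-week course.
- **That two replacements is a maximum.** Section 5.1.2 states an expectation, not a cap.
- **That 519/530 = 97.9% is the like-for-like benchmark.** Table 2 does not define its treatment failure column, and does not say whether the 9 others stopped early or whether any of the 11 did.
- **That safety summaries share the defect.** Section 10.5.3 excludes nobody.

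**Conclusion.** The point holds for failures that lead to early stopping or accompany low adherence. The direction is upward unless excluded women do as well as completers, which is least plausible for a woman stopped for breakthrough. The protocol does not fix the size. It depends on how many women are excluded and how they respond. Each worst-case exclusion costs about 6 points at this sample size, and two exclusions give an all-treated result anywhere from 15/17 to 17/17 behind a reported 15/15.

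A reader might conclude that the SVR12 objective cannot be met at all. That goes too far: the completer rate is a legitimate supportive figure. The fault is that it is the only SVR12 analysis stated, and that it stands beside a 96% whose denominator kept patients without SVR12 who were not listed as treatment failures.

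This should be fixed before analysis. It leaves the primary PK endpoint untouched.

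**What to change.** Replace the exclusion sentence in Section 10.5.2 with a rule on these lines:

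- The main SVR12 analysis includes all women who took at least one dose, replaced women included.
- Stopping for virologic breakthrough, or having no V7 HCV RNA result, counts as non-SVR12. Women stopped for other reasons are classified by their V7 result.
- The result is given as x/n with an exact 95% CI.
- The adherent-completer rate is shown as a labelled supportive analysis, with low adherence defined.

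State that replacement serves the PK set only, and reconcile the replacement rule in the Protocol Summary with that in Sections 5.1.2 and 10.3. The stopping criteria need not change for this purpose.

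The cost is wording. Section 7.5 already asks stopped women to attend their remaining visits, and V7 is timed from the last dose with HCV RNA drawn. The downside is that the reported rate may be less favourable, and that counting missing V7 results as non-SVR12 can understate response if women are lost for unrelated reasons. The supportive analysis makes that visible.
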